#### Data collection and procedures

2.3.2.

Each volunteer will be given three initial appointments to obtain relevant information and blood samples, and to perform different procedures (detailed information of the procedures developed in each appointment is provided in Table 1).

**Table 1 T1:** Information of the procedures developed in each appointment. .

Phase of study	Procedure
Baseline -core group *(App. 1, 2 & 3)*	Weight, height and body composition
	Blood pressure measurement
	Blood sample collection
	Blood sample processing
	Medical history and physical examination
	Cardiorespiratory Fitness assessment
	Online questionnaires: KIDMED, PAQ C/A, Sedentary-screentime Q, PSQ, SCOFF, DEBQ (OLQ)
	Muscular fitness assessment
	Objective assessment of PA and gait
	Data recovery and analysis
	Accelerometer removal
	Dietary intake and PA assessment
	Medical Intervention
3-month follow-up *(App. 4)*	Weight, height and body composition
	Blood pressure measurement
	Medical Follow-up
6-month follow-up *(App. 5)*	Weight, height and body composition
	Blood pressure measurement
	Blood sample collection
	Blood sample processing
	Medical history and physical examination
	Online questionnaires: KIDMED, PAQ C/A, Sedentary-screentime Q, PSQ, SCOFF, DEBQ (OLQ)
	Objective assessment of PA and gait
	Data recovery and analysis
	Accelerometer removal –after 7 days–

Each volunteer will be given three initial appointments to carry out the different proofs/questionnaires and obtain required biological samples. Those volunteers who participate in the intervention will be given two additional appointments. App., appointment.

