### Educational intervention

2.4.

To validate the biomarkers identified in the first stage of the project, an intervention study will be carried out in a subset of the core cohort. All cohort volunteers and their parents will be invited at enrolment to attend a 1 h educational session conducted by two pediatricians at the hospital. Topics covered will include the importance of weight loss in overweight/obesity and its maintenance, a therapeutic nutritional approach to childhood obesity, and the role of PA in cardiovascular fitness. A subgroup of the core cohort encompassing 25% of the participants with normal weight (NW), 25% with overweight (OW), and 50% with obesity (OB), i.e., 60 volunteers (30 for prepubertal and 30 for postpubertal groups) will be formally included in the intervention. Each volunteer participating in the intervention will be given two additional appointments to perform the different proofs/questionnaires and obtain the required biological samples (Table 1). Each individual will be his/her control, so no additional control group is required, and the results will be analyzed individually by performing a pre-post intervention statistical analysis. The number of participants to be included in the educational intervention study has been calculated to achieve a significant 0.2-point BMI *z*-score reduction between the estimated mean and the sampling mean, with a statistical power of 80% and an alpha risk of 0.05 in a one-sided test. This reduction in BMI *z*-score has been associated with a clinically significant improvement in children and adolescents with overweight (62). Potential abandonments will be compensated by incorporating more subjects from the core cohort, which is feasible since educational intervention is offered to all subjects from the core cohort (*n* = 180). A similar sample size has been used with success in previous intervention studies (63, 64).

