### Data analysis and integration

2.6.

Data will be expressed as mean ± standard deviation (SD). Data will be checked for normality using Shapiro–Wilks normality test and log-transformation will be applied when required. For multi-group comparisons depending on PA levels, body composition, or other health-related parameters available, Levene's test will be performed to assess whether the variance is equal between groups; if the variance is heterogeneous, data will be log-transformed before analysis. Regression models will be applied to analyse the complex data. Comparisons between two groups will be assessed by the appropriate test (*T*-test or the non-parametric Mann—Whitney *U*-test). When appropriate, two-way ANOVA will be used to further determine the effects of different factors, in the case of independent categorical variables. ANCOVA analyses including variables such as BMI, age and gender as covariates will be also used, when appropriate. The threshold of significance will be defined at *P* < 0.05. Correlation analyses are also envisaged to study the possible relationships between the candidate biomarkers and PA levels and other health-related parameters. SPSS and R software will be used for general statistical analyses.

Omics data from transcriptomics and miRNomics (subset of the core cohort) will be subjected to an exploratory analysis of data through principal component analysis (PCA) and partial least squares discriminant analysis (PLS-DA) (when appropriate). Analysis of differential gene expression will be performed through *T*-tests, such as Student's or limma, ANOVA, and false discovery rate (FDR) correction. Gene set enrichment analysis and functional and pathway analyses will be performed. Metabolomics datasets will also be processed using PCA and PLS-DA, and metabolite network mapping using KEGG reactant pairs along with Tanimoto similarity.

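### Replacing children who drop out restores the count of 60 but not representativeness, so the uncontrolled 6-month change may overstate the BMI z-score reduction

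*Protocol article*

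**What the plan says.** All of the following is in the protocol article.

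- **Size of phase 2** (Section 2.4): "60 volunteers (30 for prepubertal and 30 for postpubertal groups) will be formally included in the intervention". They are to be 25% normal weight, 25% overweight and 50% obesity.
- **Sample-size basis** (Section 2.4): the number "has been calculated to achieve a significant 0.2-point BMI" z-score reduction, "with a statistical power of 80% and an alpha risk of 0.05 in a one-sided test". No standard deviation, dropout rate or inflation for dropout is given.
- **Comparator** (Section 2.4): "Each individual will be his/her control, so no additional control group is required". The analysis is pre-post within child.
- **Dropout** (Section 2.4): "Potential abandonments will be compensated by incorporating more subjects from the core cohort". The article calls this feasible because all 180 cohort members are offered the intervention. It does not say whether children who leave stay in the analysis, or whether replacements keep the age split and weight mix.
- **Visits** (Table 1 and Section 2.4): weight, height, body composition and blood pressure are taken at 3 and 6 months. Blood sampling, accelerometry and questionnaires are repeated only at 6 months.
- **Biomarkers** (Sections 2.5 and 2.6.1): candidate markers are re-measured at the end of the intervention, and the score equation is tested in this subgroup after the intervention.

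**The concern.** Replacement solves a problem of numbers. The problem that dropout creates in a pre-post study is one of selection: whether a child reaches the 6-month visit may depend on how the programme is going. In a weight and activity programme, children who are not improving are plausibly the likelier to leave. Each replacement counts towards the target only by finishing, so filling the empty places adds more completers and leaves the selection as it was.

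In a controlled trial, similar selection in both arms would partly cancel. Here nothing cancels, and any difference between leavers and completers passes straight into the mean change. The sizing test is one-sided towards a fall in BMI z-score, the same direction in which losing poor responders would push the estimate.

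Two things are at stake: the size of the BMI z-score reduction that is reported, and how far the biomarker validation can be generalised beyond children who complete such a programme.

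**Working it through.** **1. The plan's own figure.** Inputs from Section 2.4: difference 0.2, one-sided alpha 0.05, power 80%, n = 60 (30 per age group). For a paired mean,

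n = [SD × (z₀.₉₅ + z₀.₈₀) / 0.2]², with z₀.₉₅ + z₀.₈₀ = 1.645 + 0.842 ≈ 2.486.

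The SD of the change is not stated, so 60 cannot be reproduced outright. Inverting the formula:

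- 60 in total: SD = 0.2 × √60 / 2.486 = 0.62 (0.616 with the t distribution)
- 30 per age group: SD = 0.2 × √30 / 2.486 = 0.44 (0.430 with the t distribution)

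Either is possible, so no error in the 60 is shown. What matters here is that the figure contains no allowance for dropout; replacement is the whole answer.

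**2. What replacement achieves.** Starters needed for 60 completers = 60 / (1 − d), where the dropout rate d is an assumption:

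| d | Starters | Leavers |
|---|---|---|
| 10% | 67 | 7 |
| 20% | 75 | 15 |
| 30% | 86 | 26 |
| 40% | 100 | 40 |

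With 180 in the cohort, 60 completers can be reached up to d = 1 − 60/180 = 67%, ignoring age and weight strata. As a device for keeping the number up, it works.

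**3. What it leaves unchanged.** Let C be the mean change in completers and L the mean change that leavers would have shown. Over all starters

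M = (1 − d) × C + d × L,

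so M − C = d × (L − C). The number of replacements does not enter. If replacements stay or leave by the same process, the completers' mean stays at C however many are added.

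**4. Size, with C = −0.20** (the plan's target, taken as the completers' result). Each cell gives M, and in brackets the amount by which the completers' mean overstates the reduction:

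| d | L = −0.20 | L = −0.10 | L = 0 | L = +0.10 |
|---|---|---|---|---|
| 10% | −0.20 (0) | −0.19 (0.01) | −0.18 (0.02) | −0.17 (0.03) |
| 20% | −0.20 (0) | −0.18 (0.02) | −0.16 (0.04) | −0.14 (0.06) |
| 30% | −0.20 (0) | −0.17 (0.03) | −0.14 (0.06) | −0.11 (0.09) |
| 40% | −0.20 (0) | −0.16 (0.04) | −0.12 (0.08) | −0.08 (0.12) |

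In the L = 0 column at 20%, 30% and 40% dropout, the overstatement is 0.04/0.20 = 20%, 0.06/0.20 = 30% and 0.08/0.20 = 40% of the target. Relative to the all-starter mean it is 0.04/0.16 = 25%, 0.06/0.14 = 43% and 0.08/0.12 = 67%.

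**5. Which outcomes can be rescued.** BMI z-score is available at 0, 3 and 6 months, so a child who leaves after the 3-month visit has a measured change. Accelerometry, questionnaires and blood markers have only baseline and 6 months. A child who leaves early has no measured change in them, whatever the analysis set.

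**The case against.** The strongest reply is that the article never says leavers are excluded. Adding children is compatible with keeping everyone who started, and the analysis set is commonly defined in a full protocol or analysis plan, neither of which is shown. That stands. A reader might infer a commitment to a completers-only analysis, but for BMI z-score the text does not make one. What remains is that replacement is the only response to dropout that is stated, and that for the 6-month-only outcomes the visit schedule itself restricts the measured change to completers.

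Second, the bias need not exist. A reader might infer that the effect is certainly overstated; the documents give no dropout rate and no outcome in leavers, and the first column of the table is zero throughout. This stands too, and the conclusion is conditional for that reason.

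Third, phase 2 is presented as a first validation of biomarkers, not as an estimate of efficacy. That limits the point: the numerical bias bears chiefly on BMI z-score. But the phase is sized on BMI z-score, and validation in completers still needs to be described as such.

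Two further readings should be set aside. From Section 2.6, "Comparisons between two groups will be assessed by the appropriate test", followed by the t-test or Mann-Whitney U, a reader might infer that the pre-post data will be tested as unpaired. That sentence follows one on comparisons between groups defined by activity level or body composition, and Section 2.4 makes each child his or her own control, so the inference fails. A reader might also infer that late replacements will have a pre-post interval longer than 6 months. The article does not say when replacements start or whether baseline is repeated, so this is conjecture.

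**Conclusion.** The point holds in conditional form. The stated handling of dropout protects the count of 60 but not its representativeness, and with no control group the 6-month change can be selected for completion. It may then overstate the BMI z-score reduction by d × (L − C). With completers at −0.20 and leavers at 0, both assumed, the overstatement is 0.04, 0.06 and 0.08 at 20%, 30% and 40% dropout. It is zero if leavers change as completers do, and larger if leavers gain. For activity and biomarker outcomes the same selection applies, but no size can be put on it from the documents. This is a worthwhile and cheap improvement, not a defect that invalidates the study.

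**What to change.** 1. State in Section 2.4 that replacements are added to the children who leave and do not displace them.
2. Analyse BMI z-score in everyone who starts the intervention, with a linear mixed model on the 0-, 3- and 6-month values: random child effect, age group, BMI group, and actual time since baseline. Actual time also covers any variation in when replacements begin.
3. Add a sensitivity analysis for BMI z-score in which leavers are given no change. The mixed model accounts for dropout related to observed values. It gains little from a child who leaves before 3 months, so this second analysis is needed.
4. Analyse the activity, questionnaire and biomarker outcomes measured only at 6 months as paired changes, and label them as results in completers. Do not impute no change for biomarkers that nobody measured.
5. Report the numbers of starters, leavers, replacements and completers, with a comparison of their baseline characteristics, including age group and weight group.

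The cost is analysis wording and a record of who started, left or joined. The 3-month weight and height are already scheduled, so no visit or assay is added. The downside is that the reported mean change may be smaller.

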### Laboratory procedures—omic analyses

2.5.

General metabolic assessment and myokines/adipokines, transcriptome, miRNAs, and metabolome analyses will be performed in plasma and PBC samples from subjects of the core cohort during the biomarker generation phase (phase 1) to provide data for subsequent integrative analysis. In particular:
-Glucose, insulin, lipid profile (total, LDL, and HDL-cholesterol; triglycerides), uric acid and creatinine levels will be evaluated in plasma samples of all subjects of the core cohort using standard automated laboratory enzymatic methods. Insulin resistance will be assessed by the homeostatic model assessment (HOMA) index.-Plasma levels of circulating myokines and adipokines of special relevance, such as contraction-induced myokines, myokines involved in muscle-adipose tissue crosstalk, and main regulatory adipokines (Irisin, Interleukin-6 and 15, myostatin, FGF21, leptin, adiponectin, etc.) will be measured using commercial assay kits based on the Luminex® xMAP® technology, and ELISA kits in all subjects of the core cohort.-Whole-genome transcriptomic analysis of PBC samples will be performed by next-generation RNA Sequencing (RNA-Seq) in a representative subset of the core cohort (90 subjects). RT-qPCR analysis of the expression of the most remarkable genes (i.e., those most physiologically plausible and affected) identified in the unbiased transcriptomic study will be used to validate the results in all subjects of the core cohort.-Combined untargeted and targeted metabolomics and lipidomics analysis of plasma will be performed in all subjects of the core cohort by a LIMeX-4D workflow with 4 different liquid chromatography–mass spectrometry (LC-MS) based methods to annotate a wide range of complex lipids, polar metabolites, and exposome compounds (mainly food components and drugs) (65, 66). Promising biomarkers originating from untargeted metabolomics/lipidomics will be quantified using the reference standardization approach (67).-For circulating miRNA analysis, RNA will be extracted from plasma samples using the RNAeasy serum/plasma Kit (Qiagen). A miRNome analysis (around 2000 miRNAs) will be assessed in plasma samples of a representative subset of the core cohort (15 of each of the 6 groups), using miRNA sequencing. The most remarkable miRNAs identified (up to 20) will be analysed in the whole cohort by RT-qPCR.Candidate biomarkers emerging from phase 1 will be measured in plasma and PBC of the subjects in the educational intervention (phase 2) study, at the end of it, using ELISA, RT-qPCR, or biochemical assays, depending on the marker, as above described.

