#### Participants

2.3.1.

A total of 180 volunteers (core cohort) will be recruited and distributed into two age groups: prepubertal individuals (*n* = 90), including children, from 8 to 10 years, and postpubertal adolescents (*n* = 90) from 13 to 15 years. Each group will include three subgroups (*n* = 30) of subjects with normal weight (NW), overweight (OW), and obesity (OB) as defined by WHO criteria (38). Volunteers will be equally distributed between both sexes in each group and subgroup. The sample size of the core cohort is based on our previous expertise in different projects aimed at identifying biomarkers (mainly gene expression biomarkers analysed in blood cells by omics techniques), in which we used even a lower number of volunteers [e.g., studies (24, 39)]. Moreover, the combination/integration of different types of biomarkers that will be performed (based not only on gene expression, but also considering lipidomic, metabolic and miRNA profiles) makes its more likely to be able to detect significant metabolic differences and more robust biomarkers. Additionally, the number of volunteers of the core cohort is also expected to be sufficient to achieve the required sample size for the intervention study, which was calculated as explained in Section 2.4.

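### RT-qPCR validation in all 180 subjects includes the 90 in whom the sequencing hits were selected, so the pooled result is not independent of discovery

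*Protocol article*

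**What the plan says.** Section 2.3.1 (Participants) sets the cohort: "A total of 180 volunteers (core cohort) will be recruited", in two age groups. "Each group will include three subgroups" of 30, one per weight class.

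Section 2.5 (Laboratory procedures—omic analyses) describes two parallel discovery steps.

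- **Genes.** RNA-Seq is done "in a representative subset of the core cohort (90 subjects". The genes taken on to RT-qPCR are described as "those most physiologically plausible and affected", and RT-qPCR of them "will be used to validate the results in all subjects of the core cohort".
- **miRNAs.** The screen is "A miRNome analysis (around 2000 miRNAs", in a "representative subset of the core cohort (15 of each of the 6 groups), using miRNA sequencing". Then: "The most remarkable miRNAs identified (up to 20) will be analysed in the whole cohort by RT-qPCR". The text does not call this step validation.

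Section 2.6 (Data analysis and integration) sets significance at P<0.05 and lists FDR correction for differential expression, without giving its level. Section 2.6.1 fits models on four fifths of the subjects and predicts the remaining fifth, ten times over. Neither section treats sequenced and unsequenced subjects separately.

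**The concern.** Markers chosen because they look strong in 90 people will tend to look strong again when re-measured in those same people, whether or not the association is real. The second assay removes some sequencing noise, but it does not redraw the subjects. Adding 90 new subjects dilutes the selection bias without removing it.

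At stake are the P value and effect size attached to each transcript or miRNA after RT-qPCR. A null marker that has been selected has much more than a 5% chance of appearing confirmed, and a true marker's effect is overstated. These candidates then feed the roughly 20-variable PA score and the phase 2 check.

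**Working it through.** **Counts from the protocol.** Cohort: 2 × 3 × 30 = 180, as stated. miRNA discovery set: 6 × 15 = 90. RNA-Seq discovery set: 90, as stated. Not sequenced, for either platform: 180 − 90 = 90. Discovery subjects are 90/180 = 50% of the set in which hits are re-tested.

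**Assumptions not in the protocol.** Two-sided testing; a correlation ρ between the sequencing and RT-qPCR values of the same subject (0.5 to 1.0); the selection threshold. For miRNAs, 20 carried forward out of about 2000 corresponds to selection at p<0.01 (20/2000 = 0.01).

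**Model for a null marker.**
- Discovery statistic in the sequenced 90: z1, selected if its two-sided p is below the threshold.
- RT-qPCR statistic in the same 90: zq = ρ·z1 + √(1−ρ²)·e, with e standard normal.
- RT-qPCR statistic in the other 90: z2, standard normal and independent of z1.
- Pooled statistic in 180: z = √0.5·zq + √0.5·z2. It counts as confirmed if |z|>1.96.

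Given z1, the pooled z has mean √0.5·ρ·z1 and variance 1 − 0.5ρ².

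**One case by hand.** A marker exactly at p = 0.01 has z1 = 2.576. With ρ = 1 the pooled mean is 0.707 × 2.576 = 1.82 and the SD is √0.5 = 0.707. The chance of passing is P(Z > (1.96 − 1.82)/0.707) = P(Z > 0.20), about 42%. With ρ = 0.5 the mean is 0.91, the SD is √0.875 = 0.935, and the chance is P(Z > 1.12), about 13%. Selected markers lie at or beyond the threshold, so the averages are higher.

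**Averaged over selected null markers (2,000,000 draws per cell): chance of P<0.05 in all 180.**

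| Selected at | ρ=1 | ρ=0.9 | ρ=0.8 | ρ=0.5 |
|---|---|---|---|---|
| p<0.05 | 34% | 28% | 22% | 12% |
| p<0.01 | 54% | 44% | 35% | 16% |
| p<0.001 | 78% | 65% | 52% | 23% |
| p<0.0001 | 91% | 80% | 67% | 30% |

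In the unsequenced 90 the rate is 5% in every cell, or 2.5% in the discovery direction.

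If all 20 miRNAs carried forward were null, the expected number confirmed in 180 would be 10.9, 8.8, 7.0 or 3.2 (ρ = 1, 0.9, 0.8, 0.5), against 1.0 in the unsequenced 90.

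**Check with subject-level data.** 2000 null features, top 20 picked in 90, ρ = 0.9. Two-group t-test: 43% pass in 180, 5.5% in the unsequenced 90. Three-group ANOVA: 38% and 4.7%.

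**Effect size.** The pooled estimate is the average of the two halves. For a null marker the expected standardised RT-qPCR effect in the sequenced half is ρ times the discovery effect, and in the other half it is zero. The pooled estimate therefore keeps a fraction 0.5ρ of the discovery effect: 25% at ρ = 0.5 and 50% at ρ = 1.

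**The case against.** **FDR correction.** This is the strongest objection. With every marker null and a Benjamini–Hochberg filter at an assumed 5%, simulated screens released any marker at all in only about 1–9% of datasets. A reader might infer from the table that 20 null markers will go forward and that a third or a half of them will be reported as validated. The documents do not support that: the percentages are conditional on a null marker having been selected. What stands is that the FDR level is not given, and that selection is described by prominence, plausibility and a cap of 20 rather than by passing an FDR threshold. FDR control also leaves the bias in whatever is selected. A stricter filter passes fewer null markers, but each is then more likely to be confirmed in 180, as the lower rows of the table show.

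**Technical validation.** RT-qPCR in sequenced samples is legitimate assay validation, the other 90 do add independent data, and measuring all 180 gives complete values for the score. All of this is right. The fault lies in naming the whole cohort as the validation set without separating the halves.

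**Scope of the text.** A reader might also infer a specified pooled validation P value, or a stated number of genes carried forward. The protocol gives neither: the cap of 20 applies to miRNAs only, and so does the absence of the word validate. Fuller analysis detail may exist elsewhere. The validation population for genes is nevertheless stated, so this is more than an omitted detail.

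**Later safeguards.** Selection by several methods, the four-fifths/one-fifth split and phase 2 mean that RT-qPCR alone does not establish a biomarker. They do not cure the overlap. A test fifth has 36 subjects, of whom about 18 on average would come from the sequenced 90. The 60 phase 2 subjects are also core-cohort members.

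**Conclusion.** The point holds for RNA-Seq hits as the protocol is written, and the miRNA step has the same structure without the label. A pooled RT-qPCR test in 180 is not independent of discovery. For a null marker selected at p<0.01, the false-confirmation rate is about 16–54%, roughly 3 to 11 times the nominal 5%. Over all thresholds tried, the range is 12–91%. These figures rest on an assumed ρ of 0.5–1.0, two-sided tests and the assumed selection thresholds.

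It would go too far to say that chance findings are bound to confirm themselves. The overlap raises the probability of false confirmation; it does not make it certain. How many null markers are exposed to it depends on how firmly selection is tied to FDR, which the protocol leaves open.

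**What to change.** Keep RT-qPCR in all 180 and change how the results are used:

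- Report the association test (P value and effect size) in the 90 unsequenced subjects as the replication result, for genes and miRNAs alike.
- Report RT-qPCR in the sequenced 90 separately, as technical concordance with sequencing.
- Label any pooled estimate in 180 as not independent of discovery.
- Where possible, sequence the same 90 subjects for RNA and miRNA. The protocol does not say that the two subsets coincide. If they were disjoint, 180 − 90 − 90 = 0 subjects would be unsequenced on both platforms.

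No new samples or assays are needed. The cost is power. Illustratively, for two equal groups (45 v 45 against 90 v 90), power is 81% against 98% at a standardised difference of 0.6, and 66% against 92% at 0.5. The plan has three PA clusters, so its own figures will differ.

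This does not create a held-out set for the full multi-omic score, because metabolomics is run in all 180.
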